## Study Identification

Unique Protocol ID: AOP2949

Brief Title: 'Optiflow + Duet' Interface' vs 'Standard' High Flow Nasal Cannula  
( OPTIMARF )

Official Title: Physiological Effects of High Flow Oxygen Therapy Using 'Optiflow + Duet'  
Interface vs 'Standard' High Flow Nasal Cannula for Acute Respiratory Failure  
After Extubation. The OPTIMARF Study.

Secondary IDs:

## Study Status

Record Verification: December 2023

Overall Status: Completed

Study Start: May 8, 2023 [Actual]

Primary Completion: June 30, 2023 [Actual]

Study Completion: July 30, 2023 [Actual]

## Sponsor/Collaborators

Sponsor: University of Padova

Responsible Party: Sponsor

Collaborators:

## Oversight

U.S. FDA-regulated Drug: No

U.S. FDA-regulated Device: No

Unapproved/Uncleared Device: No

U.S. FDA IND/IDE: No

Human Subjects Review: Board Status: Approved

Approval Number: AOP2949

Board Name: Ethical Committee of Padua University Hospital

Board Affiliation: Azienda Ospedale-Università Padova

[contact]

Email: [contact]

Address:

[name]

Data Monitoring: Yes  
FDA Regulated Intervention: No

## Study Description

**Brief Summary:** High-flow nasal cannula (HFNC) therapy is increasingly used in the management of acute respiratory failure. Its clinical application has been largely investigated in chronic obstructive pulmonary disease (COPD) patients but only marginally in patients experiencing acute respiratory failure after extubation. Promising data have been published in vitro about new asymmetrical high flow nasal cannula, named 'Optiflow + DUET'. Positive airway pressure, that dynamically changes with breathing, and clearance of anatomical dead space are the key mechanisms of noninvasive respiratory support with nasal high flow. Pressure mainly depends on flow rate and nare occlusion. The hypothesis is that an increase in asymmetrical occlusion of the nares leads to an improvement in dead-space clearance resulting in a reduction in re-breathing and breathing work.

**Detailed Description:** A prospective cross-over RCT on the effects of 'Optiflow + DUET' as compared to conventional symmetrical high flow cannula and Venturi mask.

## Conditions

**Conditions:** Hypoxemia  
**Keywords:** asymmetrical nasal cannula  
hypoxemia  
DUET

## Study Design

**Study Type:** Interventional  
**Primary Purpose:** Supportive Care  
**Study Phase:** N/A  
**Interventional Study Model:** Crossover Assignment  
**Number of Arms:** 2  
**Masking:** None (Open Label)  
**Allocation:** Randomized  
**Enrollment:** 20 [Actual]

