| 
several clinical parameters (i.e. DUS, EIT, ABGs, comfort, VAS) will be collected.
 
Specifically, Gas-flow rate will be set at a maximum of 60 L/min, temperature at a maximum of 37°C, while FiO2 will be adjusted to maintain a peripheral saturation (SpO2) between 92 and 98%.
                                                                                                                                                                                                                                                                                                                                      | 
a maximum of 37°C, while FiO2 will be adjusted to maintain SpO2 between 92 and 98%.
                                                                                                                                                                                                                                                                                                                                                                                                                                                                                                                                                                                       |

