## Outcome Measures

### Primary Outcome Measure:

1. Breathing effort  
To evaluate changes, between arms, in breathing effort (as assessed by diaphragm ultrasound (DUS)).  
[Time Frame: Last 10 minutes of 1 hour-trial]
2. Lung aeration  
To evaluate changes, between arms, in lung aeration (as assessed by the end-expiratory lung impedance (delta EELI) through EIT.  
[Time Frame: Last 10 minutes of 1 hour-trial]

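### No interface-masked measurement is provided for the diaphragm ultrasound primary outcome, so a systematic reading tendency would enter the within-patient interface difference

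*Protocol*

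**What the plan says.** The Study Design section describes a randomised trial with the model "Crossover Assignment", an actual enrolment of 20, and masking "None (Open Label". That entry makes no exception for any role, so it includes the person who assesses outcomes.

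Two primary outcomes are listed. The first is the change between arms "in breathing effort (as assessed by diaphragm ultrasound (DUS"; the second is the change between arms "in lung aeration (as assessed by the end-expiratory lung impedance (delta EELI) through EIT". Both have the time frame "Last 10 minutes of 1 hour-trial", so they are taken while the cannula under test is in use. The Arms and Interventions section adds only that at the end of each session "several clinical parameters (i.e. DUS, EIT, ABGs, comfort, VAS) will be collected".

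The Study Description states a direction: more asymmetrical occlusion of the nares should improve dead-space clearance, "resulting in a reduction in re-breathing and breathing work".

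The protocol names no ultrasound index, no reader and no reading procedure. It does not say whether ultrasound clips or EIT files are stored, and it mentions neither coded files nor offline measurement.

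**The concern.** A nasal cannula cannot be hidden from the patient or the bedside staff, so open-label treatment is not the problem. The problem is that measurement is left unmasked as well. As a matter of general measurement knowledge (the protocol does not discuss it), a diaphragm ultrasound value depends on which breath is chosen and where the measurement is placed. The protocol fixes neither the index nor a reading rule, so nothing in it limits that discretion. The first primary outcome measures the quantity that the hypothesis says should fall.

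In a crossover, each patient contributes one asymmetrical-minus-symmetrical difference. A tendency to read effort lower on the asymmetrical cannula shifts all these differences the same way. Randomising the order balances period effects, but this tendency follows the interface and not the period, so it stays. More patients would not dilute it; they would only estimate the shifted value more precisely.

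Delta EELI is less exposed. It is derived from the device signal, and a reader could influence it mainly through the choice of recording segment and reference level.

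**Working it through.** **The plan's own figures.** The protocol states no sample-size calculation, alpha, test or SD, so there is no figure to reproduce. The 20 is actual enrolment.

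**Inputs**
- n = 20 pairs: Study Design, assuming that every enrolled patient gives a value on both interfaces.
- Paired t-test, two-sided alpha 0.05: assumed.
- True interface difference of zero: assumed, so that every rejection is a false positive.
- Reading bias b, in SDs of the within-patient difference: assumed over a range. The protocol gives no value.

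**Why the bias passes through in full.** Write patient i's measured value on interface k as the true value plus a reading shift r_k. The paired difference is then d_i = (true difference)_i + (r_asym − r_sym). The last term is the same for every patient and does not involve the order of the periods. The mean of d is therefore off by r_asym − r_sym in both sequence groups, and comparing or averaging the sequences does not remove it. Expressed in SDs of d, this term is b.

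**Rejection rate.** Under these assumptions the t statistic is noncentral t with df = 19 and noncentrality b × √20. The critical value is t(0.975; 19) = 2.093. The rejection rate is P(T > 2.093) + P(T < −2.093).

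| Assumed b (SD) | Noncentrality b × √20 | Rejection rate with no true effect |
|---|---|---|
| 0 | 0 | 5.0% |
| 0.1 | 0.447 | 7.1% |
| 0.2 | 0.894 | 13.6% |
| 0.25 | 1.118 | 18.6% |
| 0.3 | 1.342 | 24.7% |
| 0.5 | 2.236 | 56.5% |

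**Scale.** With 20 pairs and the same test, the true effect detectable with 80% power is 0.66 SD of the paired difference. A bias of 0.25 SD is therefore 0.25 / 0.66 ≈ 38% of the smallest effect that the trial could reliably detect.

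**What masked reading would change.** If measuring with the interface hidden brings the reading part of b to zero, the rate attributable to reading returns to 5.0%. A shift that arises while the images are acquired at the bedside remains.

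**The case against.** The strongest objection is that this is a small open-label physiological crossover with a visible device, already completed, and that the protocol does not show that anything went wrong. Much of this stands.

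- **Storage is not documented.** The protocol says only that the measurements are collected. That clips or raw EIT files exist is an assumption, and so is the low cost of re-reading them.
- **The reader is not identified.** The protocol does not say that the bedside operator chose the values. It only fails to provide for anyone masked.
- **The bias sizes are not sourced.** Neither the range of b, nor the alpha, nor the test comes from the document. The 56% figure shows what a half-SD bias would do, not that one is plausible.
- **Masked reading is a partial remedy.** If the breath is frozen at the bedside, that choice is already made. With 20 patients, the same operator might also recognise images.

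Three stronger readings are tempting and are not supported. A reader might infer that expectation did produce the primary result; the document contains no result and no estimate of bias. A reader might infer that both primary outcomes are equally compromised; delta EELI is device-derived, and the protocol does not say whether a person chooses its segment or reference. A reader might infer that the bias is beyond repair; if recordings survive, its reading part can still be removed.

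The core is untouched by these points. The masking entry makes no exception for the assessor, no section provides masked reading, and the hypothesis has a direction. Nor can this be left to the analysis plan: masking is a matter of conduct, and analysing values that were read with the interface known does not make them masked.

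**Conclusion.** The point holds for the first primary outcome, "To evaluate changes, between arms, in breathing effort (as assessed by diaphragm ultrasound (DUS"), and in a weaker form for delta EELI. The design leaves the DUS comparison open to a reading bias that order randomisation does not cancel, and the protocol contains no safeguard against it.

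Its size cannot be derived from the document. Under the assumptions set out above, the false-positive rate would rise from 5% to about 7%, 19% or 56% for assumed biases of 0.1, 0.25 or 0.5 SD. These figures show how sensitive a 20-patient paired comparison is; they do not estimate what happened. The conclusion rests on the absence of any masked reading in the protocol and on the general operator dependence of ultrasound, not on the upper end of that range.

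This is an avoidable weakness that should be addressed. It is not evidence that the trial's result is wrong.

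**What to change.** **As a design provision.** Save the DUS clips and the EIT recordings of the last 10 minutes of each session under a code. Have the existing operator measure them afterwards in random order, with patient, interface and period hidden. Set masking to 'Outcomes Assessor' for these outcomes only if this is done. Keep comfort and dyspnea labelled as unmasked, since patients rate them knowing the interface.

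**For this trial, which is listed as completed:**
- If masked reading was done, correct the masking entry and describe the procedure.
- If it was not done but recordings exist, carry out the masked re-reading and report it as such.
- If no recordings exist, leave the masking entry as it is and report unmasked reading of the primary outcome as a limitation.

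**Cost.** For the two interfaces, 20 patients × 2 = 40 sessions have to be read for each modality, or 60 if the Venturi mask baselines are included. If the files were kept, this needs no new patients, procedures or staff.

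**Downsides.** Results come later, the same operator may recall some images, and bias from bedside image acquisition is not removed. The report should state the last two.

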## Arms and Interventions

| Arms                                                                                                                                                                                                                                                                                                                                                                                      | Assigned Interventions                                                                                                                                                                                                                                                                                                                                                                                                                                                                |
|-------------------------------------------------------------------------------------------------------------------------------------------------------------------------------------------------------------------------------------------------------------------------------------------------------------------------------------------------------------------------------------------|---------------------------------------------------------------------------------------------------------------------------------------------------------------------------------------------------------------------------------------------------------------------------------------------------------------------------------------------------------------------------------------------------------------------------------------------------------------------------------------|
| Active Comparator: Symmetrical high flow nasal cannula (HFNO)
After a 'baseline' trial using Venturi Mask, within the first 120 minutes after extubation, and assessing a arterial oxygen pressure (PaO2) and inspiratory oxygen fraction (FiO2) ratio < 300, patients will be randomly assigned to a first 1h-phase of 'conventional HFNO' or 'DUET HFNO'. At the end of each session | Device: Symmetrical high flow nasal cannula (HFNO)
After a 'baseline' trial using Venturi Mask, within the first 120 minutes after extubation, and assessing a PaO2/FiO2 ratio < 300, patients will be randomly assigned to a first 1h-phase of 'conventional HFNO' or 'DUET HFNO'. At the end of each session several clinical parameters (i.e. DUS, EIT, ABGs, comfort, VAS) will be collected. Specifically, Gas-flow rate will be set at a maximum of 60 L/min, temperature at |

| Arms                                                                                                                                                                                                                                                                                                                                                                                                                                                                                                                                                                                                                                 | Assigned Interventions                                                                                                                                                                                                                                                                                                                                                                                                                                                                                                                                                                                                                                                           |
|--------------------------------------------------------------------------------------------------------------------------------------------------------------------------------------------------------------------------------------------------------------------------------------------------------------------------------------------------------------------------------------------------------------------------------------------------------------------------------------------------------------------------------------------------------------------------------------------------------------------------------------|----------------------------------------------------------------------------------------------------------------------------------------------------------------------------------------------------------------------------------------------------------------------------------------------------------------------------------------------------------------------------------------------------------------------------------------------------------------------------------------------------------------------------------------------------------------------------------------------------------------------------------------------------------------------------------|
| 
several clinical parameters (i.e. DUS, EIT, ABGs, comfort, VAS) will be collected.
 
Specifically, Gas-flow rate will be set at a maximum of 60 L/min, temperature at a maximum of 37°C, while FiO2 will be adjusted to maintain a peripheral saturation (SpO2) between 92 and 98%.
                                                                                                                                                                                                                                                                                                                                      | 
a maximum of 37°C, while FiO2 will be adjusted to maintain SpO2 between 92 and 98%.
                                                                                                                                                                                                                                                                                                                                                                                                                                                                                                                                                                                       |
| 
Active Comparator: Asymmetrical high flow nasal cannula (DUET HFNO)
 
After a 'baseline' trial using Venturi Mask, within the first 120 minutes after extubation, and assessing a PaO2/FiO2 ratio < 300 (as described above), patients will be randomly assigned to a second 1h-phase of 'DUET HFNO' vs 'conventional HFNO'. At the end of each session several clinical parameters (i.e. DUS, EIT, ABGs, comfort, VAS) will be collected.
 
Specifically, Gas-flow rate will be set at a maximum of 60L/min, temperature at a maximum of 37°C, while FiO2 will be adjusted to maintain SpO2 between 92 and 98%.
 | 
Device: Asymmetrical high flow nasal cannula (DUET HFNO)
 
After a 'baseline' trial using Venturi Mask, within the first 120 minutes after extubation, and assessing a PaO2/FiO2 ratio < 300, patients will be randomly assigned to a first 1h-phase of 'DUET HFNO' vs 'conventional HFNO'. At the end of each session several clinical parameters (i.e. DUS, EIT, ABGs, comfort, VAS) will be collected. Specifically, Gas-flow rate will be set at a maximum of 60 L/min, temperature at a maximum of 37°C, while FiO2 will be adjusted to maintain SpO2 between 92 and 98%. A 5-10min 'washout' phase using VM, between different interfaces, will be allowed.
 |

## Outcome Measures

### Primary Outcome Measure:

1. Breathing effort  
To evaluate changes, between arms, in breathing effort (as assessed by diaphragm ultrasound (DUS)).  
[Time Frame: Last 10 minutes of 1 hour-trial]
2. Lung aeration  
To evaluate changes, between arms, in lung aeration (as assessed by the end-expiratory lung impedance (delta EELI) through EIT.  
[Time Frame: Last 10 minutes of 1 hour-trial]

### Secondary Outcome Measure:

3. Minute ventilation (MV) (L/min)  
To evaluate breathing pattern  
[Time Frame: Last 10 minutes of 1 hour-trial]
4. corrected MV (L/min)  
To evaluate breathing pattern  
[Time Frame: Last 10 minutes of 1 hour-trial]
5. Breathing heterogeneity  
To evaluate changes, between arms, in ventilation distribution (as assessed by pendelluft (yes/not), respiratory rates/min, tidal volume (ml), global inhomogeneity index through EIT)  
[Time Frame: Last 10 minutes of 1 hour-trial]
6. Comfort  
To evaluate changes in comfort, between arms, as assessed by NRS scale  
[Time Frame: Last 10 minutes of 1h-trial]
7. Dyspnea  
To evaluate changes in dyspnea, between arms, as assessed by VAS scale  
[Time Frame: Last 10 minutes of 1h-trial]

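### Secondary outcome 5 records pendelluft only as present or absent in 20 crossover patients; a graded value from the same EIT recording would be more informative

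*Protocol*

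**What the plan says.** The Protocol, under Secondary Outcome Measure, gives the aim of outcome 5 (Breathing heterogeneity) as "To evaluate changes, between arms, in ventilation distribution". Four items are listed for it: "as assessed by pendelluft (yes/not), respiratory rates/min, tidal volume (ml), global inhomogeneity index through EIT". The measurement window is the last 10 minutes of each one-hour session. Outcomes 3 and 4, minute ventilation and corrected minute ventilation, carry a different aim: "To evaluate breathing pattern".

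Study Design states "Interventional Study Model: Crossover Assignment" and "Enrollment: 20 [Actual"], so there are at most 20 within-patient pairs. Arms and Interventions lists EIT among the measurements collected at the end of each session. Study Status shows the trial as completed in July 2023.

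The protocol gives no significance level, no expected pendelluft prevalence, no effect size and no criterion for calling pendelluft present.

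**The concern.** Reducing a measurement to two categories discards the size of the change within each patient. In a paired design the loss is sharp: a patient with pendelluft on both cannulas, or on neither, adds nothing to the test, even if its amplitude halves. With 20 pairs there may be very few informative patients. A moderate reduction with the asymmetrical cannula could then be reported as no difference simply because of how the item was coded.

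A lesser matter is what the outcome groups together. Respiratory rate and tidal volume are whole-lung quantities and carry no information on where the gas goes. Their product is minute ventilation, which the protocol itself files under breathing pattern. A change in either one is not evidence about ventilation distribution.

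**Working it through.** The protocol gives no power or sample-size figure, so there is nothing to reproduce. The question is how much a yes/no record can show with 20 pairs.

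**Inputs.** From the protocol: 20 patients, crossover, pendelluft binary. Assumed, because not stated: two-sided 0.05; pendelluft prevalence 20–60% on one cannula; within-patient correlation 0.3–0.7; a paired shift of 0.66 SD of the within-patient difference, chosen because a paired t-test with 20 pairs detects it with 80% power (noncentral t, 19 df).

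**Step 1: smallest significant result.** With b patients switching one way and c the other, the exact McNemar p-value is 2 × P(X ≤ min(b, c)), with X binomial(b + c, 0.5).
- 5:0 gives 2 × 0.5^5 = 0.063.
- 6:0 gives 2 × 0.5^6 = 0.031.
- 7:1 gives 0.070 and 8:1 gives 0.039.

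So at least 6 of 20 patients (30%) must switch, all in one direction. A single reverse switch raises the requirement to 9 switchers.

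**Step 2: power in terms of switching.** Summing the trinomial probabilities over all significant tables:

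| Switch one way | Switch other way | Net | Power |
|---|---|---|---|
| 25% | 5% | 20 points | 20% |
| 35% | 5% | 30 points | 46% |
| 45% | 5% | 40 points | 69% |

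Reaching 80% takes a net change of about 37 points with no reverse switches, 46 points with 5% reverse and 54 points with 10% reverse.

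**Step 3: yes/no against a fully graded value.** Let the latent amplitude be bivariate normal with correlation ρ, shifted by 0.66 × √(2(1 − ρ)) between cannulas, and cut at the stated prevalence. At ρ = 0.5 and 40% prevalence the shift is 0.66 × √1 = 0.66. The switching probabilities are then 27.3% and 5.4%, and McNemar power is 24%. Over the grid, power runs from 3% (ρ = 0.7, prevalence 20%) to 40% (ρ = 0.3, prevalence 60%). The graded value has 80% throughout by construction.

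**Step 4: a less favourable model for the graded value.** Pendelluft amplitude may be zero in many patients. Setting everything below the cut to zero, at ρ = 0.5 and the same shift, simulation gives approximately:

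| Prevalence | Graded, signed-rank | Yes/no, McNemar |
|---|---|---|
| 20% | 10% | 6% |
| 40% | 40% | 24% |
| 60% | 58% | 32% |

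The graded value is better in every row, but the 80% benchmark is not reached.

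**Step 5: the rest of outcome 5.** The global inhomogeneity index is continuous. With 20 pairs it has 80% power at a standardized paired difference of 0.66 and 56% at 0.5. Nothing above applies to it.

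**The case against.** **The outcome as a whole.** A reader might infer that all of outcome 5 has little power. The protocol does not support that, because the global inhomogeneity index sits in the same outcome, measures distribution directly and keeps ordinary paired power. This objection stands in full.

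**A wrong-reason finding.** A reader might also infer that a fall in respiratory rate alone would count as changed distribution. No rule is written under which any one item suffices. Four measurements are listed and each can be reported under its own name. A hierarchy or combining rule is commonly left to a statistical analysis plan, which is not shown. Nor does a multiplicity count help: moving respiratory rate and tidal volume elsewhere leaves the number of tests in the trial unchanged. Reporting them beside minute ventilation is not counting one change twice either, since rate and tidal volume can move in opposite directions while their product stays the same. What remains is the mismatch between those two items and the stated aim.

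**The assumptions.** Prevalence, correlation, effect size and significance level are all supplied here, and a normal amplitude is doubtful if many values are zero. That limits the size of the gain, as Step 4 shows, but not its direction. It is also fair that a very large change, about 37 points net with no reverse switches, would be detected with 80% power even as yes/no.

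**Feasibility.** The protocol does not say how presence is judged, how many breaths were recorded or whether recordings were stored. Re-analysis therefore depends on what was kept.

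**Conclusion.** The point holds for the pendelluft item. Fixed as yes/no in 20 pairs, it needs at least 6 one-way switchers to reach significance. Under the assumed 0.66 SD shift it has 3–40% power over the range examined. A graded value does better under both models: 80% if amplitude is normal, and roughly 10–58% against 6–32% if it is censored at zero with correlation 0.5. At the lowest prevalence neither version is informative. A non-significant yes/no result should not be read as absence of effect.

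The grouping of respiratory rate and tidal volume under ventilation distribution is a minor labelling matter. It does not show that a false conclusion was planned or drawn. Both primary outcomes are unaffected. This is a worthwhile, low-cost improvement to one item of one secondary outcome.

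**What to change.** In outcome 5, analyse pendelluft as a graded within-patient value from the end-of-session EIT recording. Use amplitude as a percentage of the tidal impedance change or, if only presence can be flagged breath by breath, the percentage of breaths showing it. Compare the two cannulas by a signed-rank test on the within-patient differences. Keep the yes/no count as description and state the criterion used for it.

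Base any statement about ventilation distribution on pendelluft and the global inhomogeneity index. Report respiratory rate and tidal volume with outcomes 3 and 4. This is relabelling and does not change the number of tests.

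The cost is some additional offline EIT analysis and no extra patients, provided the recordings are stored in usable form. If they are not, keep pendelluft as a descriptive count only. Because the trial is completed, the changed definition must be disclosed as post hoc, with the yes/no result reported beside it.
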